### **Trial Management Group (TMG)**

This group will oversee the day-to-day running of the trial and the members will be primarily the clinical and data management teams. The members will be the clinical co-ordinator, study nurse and data manager. The Microbiologists will join if there are relevant items on the agenda. Notes will be taken and will form the basis of the progress report to the Trial Coordinating Committee.

### **HIVIS Governing Board**

The HIVIS Governing Board will review the notes from the TCC meetings regarding progress of the trial, and will be meeting once a month.

### **Data and Safety Monitoring Board (DSMB)**

An independent Data and Safety Monitoring Board will be appointed by the sponsor of the study, MUHAS and SMI. The role of the DSMB will include;

1. To review the research design and the plans for data and safety monitoring
2. To receive and review at intervals the progress reports from the investigators
3. To monitor safety data
4. To monitor and evaluate trial progress, including
  - a. Periodic assessment of data quality and timelines
  - b. Performance of the study sites
5. To recommend to the sponsor, local IRBs and investigator concerning continuation or to stop the study.

The DSMB will meet whenever a safety report has been submitted and make a recommendation to the TCC within 7 days as to the future conduct of the trial.

They will also meet on one occasion to review the safety data, after half the volunteers have received the first immunization in order to make recommendations to the sponsors of the study.

### **Community Advisory Board**

There will also be a Community Advisory Board drawing members mainly from the Police Force. There may also be members from the media as well as legal representation. In addition, the wider Tanzanian community has since the first high profile National HIV vaccine Strategy Plan Workshop held in Bagamoyo in 2001 been informed through the mass media on the need and on plans for HIV vaccine trials in Tanzania. The public will continue to be informed through press releases and through other channels on all the stages of the HIVIS trial.

### **INDICATIONS FOR ADDITIONAL REVIEW**

There will be an additional meeting if 3 or more volunteers experience an unexplained, unexpected grade 3 or 4 clinical or laboratory event (confirmed on attendance or repeat testing) not resolved within 72 hours and considered probably or possible and likely to be related to vaccine product.

### **STATISTICAL CONSIDERATIONS**

By the end of this study 60 volunteers will have been exposed to DNA or placebo as well as MVA or saline placebo and described in the quantitative and qualitative immunogenicity and safety evaluation.

#### *Analysis*

All safety end-points will be graded by the Clinical Investigator and reviewed by the Trial Management Group. Any queries about grade and relationship to study product that cannot be resolved will be referred to the Trial Coordinating Committee for a final decision.

#### *The primary end-points are:*

1. The safety of immunization with the seven DNA plasmids carrying HIV-1 genes as assessed by clinical signs, and standard biochemical/haematological laboratory tests where any worsening of the severity grade will be considered for causality by the vaccine

2. A qualitative and quantitative evaluation of the magnitude and quality of humoral (neutralizing and binding antibodies, by serology) as well as cellular (cytotoxic T-cell, IFN-gamma by ELISPOT, T-cell proliferation (Fascia) and intracellular cytokines by flow cytometry) immune responses as elicited by the different schedules of immunization

The alternative routes of immunization (im and id with the Bioject device) will be evaluated for adverse events by assessing local (pain, cutaneous including induration), general (fever, chills, headache, nausea, vomiting, malaise, myalgia) and other unsolicited adverse events within 7 days. Any grade 3 or 4 event will be taken as an indication that the arm is less tolerable

*The secondary endpoints are:*

1. A qualitative and quantitative assessment on the presence of necessary infrastructure and human capacity to conduct HIV-related vaccine studies at MUHAS.

### **Statistical analysis**

The final analysis will be conducted once all study participants have received all their immunizations and completed a 24 weeks follow-up period, or have permanently withdrawn from the study. Safety analyses will further be updated in the event that there is a 52 weeks follow up. Analyses will be based on the principle of intention-to-treat.

### **Volunteer characteristics**

Baseline characteristics will be summarized by study arms, using appropriate summary statistics. Study participant characteristics to be summarized will include demographic variables and baseline values relevant to safety and immunogenicity.

### **Safety data**

The number and percentage of subjects experiencing any adverse events (AE), grade 3 or 4 adverse events, serious adverse events (SAE), and the number of events reported, will be summarized by severity and reported relationship to study treatment for each treatment group, both for all adverse events and by type of adverse event. Calculation of incidence rates of adverse events will include each subject only once, either according to worst severity or first reported event.

Rates of the various adverse events will be compared between the study arms using Fisher's exact test. Rates will be summarized using exact binomial confidence intervals

Safety haematological and biochemical laboratory parameters will be summarized at each study visit according to study arm. Comparisons will be done using 2-sample t-tests or non-parametric equivalents as appropriate to the data

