#### Study Design

Randomised, controlled, double blinded study. The laboratory staff will also be blinded to the immunization regimens.

| Arm  | Volunteers | DNA immunization                     | MVA boost                               |
|------|------------|--------------------------------------|-----------------------------------------|
| I    | 20         | DNA 3.8mg intramuscularly by Bioject | MVA 10  pfu intramuscularly |
| II   | 20         | DNA 1.0mg intradermally by Bioject   | MVA 10  pfu intramuscularly |
| IIIa | 10         | Saline intramuscularly by Bioject    | Saline i.m                              |
| IIIb | 10         | Saline id by Bioject                 | Saline i.m                              |

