## **Immunizations**

### ***Immunization schedule***

While DNA immunizations will be performed at weeks 0, 4 and 12. 1st MVA will be given at weeks 36 and the 2nd MVA will be given at week 80. The immunization schedule is summarized below:

| Weeks                | -4-8 | -2-4 | 0    | 2 | 4    | 6 | 8 | 12   | 14 | 16 | 36    | 38 | 40 | 44 | 60 | 64     | 76 | 78 | 80    | 82 | 84 | 88 | 104 | 106    |
|----------------------|------|------|------|---|------|---|---|------|----|----|-------|----|----|----|----|--------|----|----|-------|----|----|----|-----|--------|
| Visits               | 1    | 2    | 3    | 4 | 5    | 6 | 7 | 8    | 9  | 10 | 11    | 12 | 13 | 14 | 15 | 16     | 17 | 18 | 19    | 20 | 21 | 22 | 23  | 24     |
| Type of immunization |      |      | DNA1 |   | DNA2 |   |   | DNA3 |    |    | MVA 1 |    |    |    |    | EXIT 1 |    |    | MVA 2 |    |    |    |     | EXIT 2 |

| Arm         | Volunteers | DNA immunization                  | MVA boost               |
|-------------|------------|-----------------------------------|-------------------------|
| I    | 20         | DNA intramuscularly by Bioject    | MVA 10  i.m |
| II   | 20         | DNA id by Bioject                 | MVA 10  i.m |
| IIIa | 10         | Saline intramuscularly by Bioject | Saline i.m              |
| IIIb | 10         | Saline id by Bioject              | Saline i.m              |

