## Doses

| Vaccine and delivery method | Route           | Ampoule 1 (env), Left arm               | Ampoule 2 (gag, Rtmult), Right arm      |
|-----------------------------|-----------------|-----------------------------------------|-----------------------------------------|
| DNA by Biojector            | Intramuscularly | 1.0 ml (tot 2.0 mg DNA)                 | 0.9 ml (tot 1.8 mg DNA)                 |
| DNA by Biojector            | Intradermally   | 3 injections of 100ul (Total 0.6mg DNA) | 2 injections of 100ul (total 0.4mg DNA) |

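### The safety analysis leaves precision unused: laboratory tests omit the pre-vaccination value, and adverse events are neither split by vaccine phase nor pooled for the common MVA boost

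*Protocol*

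**What the plan says.** All of this is in the protocol; no SAP is shown.

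- **Adverse events (Safety data).** Events are summarised by treatment group. "Rates of the various adverse events will be compared between the study arms" by Fisher's exact test, and "Rates will be summarized using exact binomial confidence intervals". For incidence, each volunteer enters once, by worst grade or first report. The section names no pairs of arms and no split by injection or by vaccine.
- **Laboratory values (Safety data).** "Safety haematological and biochemical laboratory parameters will be summarized at each study visit according to study arm". The next sentence reads "Comparisons will be done using 2-sample t-tests or non-parametric equivalents as appropriate to the data". No baseline covariate or change from baseline is mentioned.
- **Arms (Synopsis, Study Design; Immunization schedule).** Arm I (20) is primed with "DNA 3.8mg intramuscularly by Bioject" and arm II (20) with 1.0 mg intradermally. The placebo arms are IIIa (10, saline i.m.) and IIIb (10, "Saline id by Bioject"). Arms I and II then receive the same MVA dose by the same route, and IIIa and IIIb both receive saline i.m. Each volunteer is scheduled for three DNA or placebo and two MVA or placebo injections.
- **Pre-vaccination values (Safety laboratory tests, under Screening).** Liver and renal function, glucose and a full blood picture are obtained before the first injection. Volunteer characteristics says that baseline safety values will be described by arm. End Points says that a worsening of grade will be considered for causality.

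**The concern.** With 60 volunteers in four arms, precision is scarce, and two features of the design could supply more of it.

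First, every volunteer has a pre-vaccination value for the main laboratory parameters. A two-sample test of later values leaves between-person variation in the error term that the screening value could partly explain.

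Second, the MVA boost does not differ between arms I and II. By-arm reporting alone describes MVA safety in groups of 20 when up to 40 volunteers receive the same product. Counting each volunteer once over the whole schedule, with no phase split, also puts a reaction to DNA and a reaction to MVA into the same rate. The reader then cannot tell which product the rate describes.

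A third, smaller matter is that the contrasts for DNA-phase local reactions are not named, although the design provides a placebo for each route.

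**Working it through.** The protocol gives no power, significance level, effect size or interval width for safety, so there is no stated figure to reproduce. Arm sizes agree with the total: 20 + 20 + 10 + 10 = 60. A 95% level and a two-sided 0.05 test are assumed throughout. All event rates and correlations below are assumptions.

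**1. Laboratory comparison.** If the pre-vaccination value has correlation r with the later value, adjustment multiplies the standard error by √(1 − r²), ignoring the degree of freedom spent.

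| r (assumed) | √(1 − r²) | Reduction in SE |
|---|---|---|
| 0.3 | 0.95 | 5% |
| 0.5 | 0.87 | 13% |
| 0.7 | 0.71 | 29% |
| 0.8 | 0.60 | 40% |

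For 20 v 20 and a true difference of 0.8 SD, power is 0.72 unadjusted, 0.83 with r = 0.5 and 0.94 with r = 0.7. The r = 0.3 row is shown because screening lies 4 to 8 weeks before week 0, while MVA is given at weeks 36 and 80. The correlation may therefore be weaker at late visits.

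**2. MVA phase.** Pooled sizes are 20 + 20 = 40 vaccine and 10 + 10 = 20 placebo.

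- Exact upper limit with no events, 1 − 0.025^(1/n): n = 20 gives 16.8%; n = 40 gives 8.8%.
- Chance of at least one event at a true rate of 5%, 1 − 0.95ⁿ: n = 20 gives 64%; n = 40 gives 87%.
- Fisher power by full enumeration:

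| True rates (assumed) | 20 v 10 | 20 v 20 | 40 v 20 |
|---|---|---|---|
| 50% v 10% | 0.54 | 0.74 | 0.89 |
| 60% v 20% | 0.45 | 0.65 | 0.81 |
| 30% v 5% | 0.15 | 0.45 | 0.64 |

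Forty is a maximum. The second boost needs fresh consent, so fewer may receive it.

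**3. DNA-phase local reactions, only if the placebos were pooled.** The Doses table gives one i.m. injection per side, two in all, and 3 + 2 = 5 i.d. injections. Suppose DNA adds nothing and saline reaction rates differ by route. The chance that Fisher's test rejects is:

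| Saline rate i.m. / i.d. (assumed) | I v pooled placebo | II v pooled placebo | I v IIIa | II v IIIb |
|---|---|---|---|---|
| 10% / 60% | 35.1% | 20.7% | 1.3% | 3.1% |
| 20% / 50% | 10.8% | 8.5% | 2.2% | 2.6% |

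Matching costs precision for a single arm: √(1/20 + 1/10) = 0.387, against √(1/20 + 1/20) = 0.316 with both placebo arms as control. Averaging the two matched differences with equal weights gives √(0.25 × 2 × (1/20 + 1/10)) = 0.274. That equals the 40 v 20 value, √(1/40 + 1/20) = 0.274.

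**The case against.** A reader might infer that the plan disregards its route-matched placebos and therefore produces confounded reaction contrasts. The text does not support that. IIIa and IIIb are listed as separate arms, so a comparison between arms allows I v IIIa and II v IIIb. No safety sentence says that the placebos will be pooled. The description of the randomisation envelopes seems to count IIIa and IIIb as one group, but it concerns allocation and does not govern the analysis. The contrast is unspecified, and an SAP may well specify it. The third calculation is therefore conditional on a choice the protocol has not made.

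Other objections have force:

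- Unadjusted two-sample tests are unbiased under randomisation. Pre-vaccination values are not ignored altogether, because they are described by arm and inform the review of grade changes. The primary laboratory safety parameter is a confirmed event of grade 3 or above, which a comparison of means does not address.
- The text requires laboratory summaries at each visit. That formal tests are run at every visit is a likely reading, but it is not stated.
- The common boost does not bias I v II after MVA. By-arm reporting suits the rule that judges an arm by its grade 3 or 4 events, and counts given by arm can be added up by the reader.
- Pooling assumes that priming by 3.8 mg i.m. or 1.0 mg i.d. does not change reactions to MVA.

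These points remove any claim of bias. They leave two things standing: the stated laboratory test is a less precise choice than the data allow, and the incidence rule has no phase split, so by-arm totals cannot be added into an MVA-specific rate unless events are separated first.

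**Conclusion.** The point holds as one of precision and clarity. The laboratory comparison gives up about 13% to 40% of the standard error if r is 0.5 to 0.8, and less if the correlation is weaker at late visits. By-arm reporting alone leaves the zero-event upper limit for MVA at 16.8% where 8.8% is available with all 40 boosted. It also leaves the chance of seeing a 5% event at 64% instead of 87%. The MVA figures assume that priming route and dose do not alter reactions to MVA. Neither the laboratory tests nor the by-arm reporting introduces bias. For DNA-phase local reactions the only finding is that the contrasts would be better named. Mixing of route with vaccine effect would arise only if the placebos were pooled or routes crossed, and if saline reactions differ by route.

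**What to change.** Amend Safety data as follows.

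1. **Laboratory values.** Replace the two-sample tests with a baseline-adjusted comparison for each parameter: ANCOVA, or one repeated-measures model over visits, with the pre-vaccination value as covariate. Transform or use ranks where the distribution requires it. Keep the grade-based tables as the main safety display.
2. **Adverse events by phase.** Count each volunteer once within the DNA phase and once within the MVA phase, and keep the whole-study count as a supplement.
3. **MVA phase.** Add I+II v IIIa+IIIb, with exact intervals and Fisher's test, beside the by-arm display. State how many received each boost.
4. **Clarification for DNA-phase local reactions.** Name I v IIIa and II v IIIb, or a route-stratified exact test.

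The cost is wording and programming, with no new data or volunteers. There are two drawbacks. Pooling rests on the assumption about priming, which the by-arm display lets readers check, though only roughly at 20 per arm. The matched DNA contrasts rest on 10 placebo recipients each, so single-route power is low (0.54 at 50% v 10%); the stratified test offsets this for the overall vaccine effect.

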### **Immunogenicity Data**

Immunogenicity endpoints will be compared formally at week 0, 10 and 12, according to study dosing group. Binary endpoints will be compared using Fischer's exact test. Continuous endpoints will be compared using 2-sample t-tests or non-parametric equivalents as appropriate to the data.

Immunogenicity of the candidate vaccine will be determined based on comparisons between study treatment arms. Associations between immunogenic endpoints will be assessed using multivariate regression models.

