### **A Phase I HIV-1 vaccine trial in Sweden**

A randomized, open label, phase I trial to assess the safety of different modes of administering the same DNA vaccine candidate (a plasmid DNA with inserted HIV genes env, rev, gag and RT) has recently been completed in Stockholm, Sweden. The combination of HIV-DNA and HIV-MVA proved safe and highly immunogenic. Thirty four out of 37 vaccinees (92%) having valid assays became positive in the IFN gamma ELISPOT assay, thirty-one vaccinees reacted to Gag peptide pools (p17 and p24) and 24 to Env peptide pools (gp120 and gp41). Including other assays identifying HIV-specific immunity, all but one vaccinee, 37/38 (97%), developed HIV-specific immune responses. All DNA injections were delivered by the Bioject needleless device as is happening with the current HIVIS03 trial in Dar es Salaam, Tanzania. Preliminary analysis indicate that  $\frac{1}{4}$  of the DNA given id primed equivalently to a 3.8mg dose given im, and that boosting with HIV-MVA can be achieved in volunteers despite remote small pox immunization. It was also shown that  $10^8$  pfu HIV-MVA im gave a better boosting of the HIV-DNA priming than did  $10^7$  pfu given id. Furthermore, volunteers below the age of 40 years exhibited higher levels of immune responses as compared to the other volunteers (>40 years) whose immune responses were markedly dampened (67).

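### Responder rates are compared only by Fisher's exact test; at 20 v 20 Boschloo's exact test holds the same 5% error and is never less powerful, by a margin that depends heavily on the evaluable numbers

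*Protocol*

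**What the plan says.** In the Protocol, the Immunogenicity Data section under Statistical Considerations names one test for all binary immunogenicity endpoints: "Binary endpoints will be compared using Fischer's exact test". The same section makes the arm contrasts the basis of the conclusion: "Immunogenicity of the candidate vaccine will be determined based on comparisons between study treatment arms".

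The Study Design table gives 20 volunteers to arm I ("DNA 3.8mg intramuscularly by Bioject"), 20 to arm II ("DNA 1.0mg intradermally by Bioject") and 10 to each of the placebo groups IIIa and IIIb. The Cellular responses section defines ELISPOT responders by cut-off, so responder status is a binary endpoint. Immunogenicity is one of the two primary objectives.

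For safety, the Safety data section uses the same test ("Rates of the various adverse events will be compared between the study arms using Fisher's exact test") and adds intervals: "Rates will be summarized using exact binomial confidence intervals".

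No significance level, sidedness, target power or effect size is stated. The Statistical Considerations section opens with the total only: "By the end of this study 60 volunteers will have been exposed to DNA or placebo".

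**The concern.** Fisher's test conditions on the total number of responders. With two arms of 20 the conditional distribution has few possible values, so the rejection region cannot come close to 5% and part of the permitted error goes unused. An unconditional exact test takes the worst case over the unknown common response rate and can use more of that error while still guaranteeing the level.

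This matters here because enrolment is closed at 60, so power can no longer be raised by adding volunteers. Whether intramuscular and intradermal priming give different responder rates is a contrast with only 20 per arm, and the test is one of the few things that can still be changed. The Protocol itself names the test, so this is a stated choice and not something left open for a later analysis plan.

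**Working it through.** The plan has no power or size figure of its own to reproduce.

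**Inputs.** n = 20 in arm I and 20 in arm II (Study Design table; the analysis is by intention to treat). Level: two-sided 5%, an assumption. Response rates: assumed mid-range pairs. For orientation, the Protocol reports 19/46 = 41.3% ELISPOT responders across all arms after DNA priming in this trial, and 34/37 = 92% in the Swedish trial.

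**Method.** List all 21 × 21 = 441 tables (a responders of 20, b responders of 20).

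- Fisher: reject if the two-sided conditional p ≤ 0.05.
- Boschloo: the p-value of a table is the maximum, over a common rate π from 0.001 to 0.999, of the total probability of all tables whose Fisher p is no larger. Reject if ≤ 0.05.
- Size: max over π of Σ Bin(a; 20, π) · Bin(b; 20, π), summed over rejected tables.
- Power: Σ Bin(a; 20, p₁) · Bin(b; 20, p₂), summed over rejected tables.

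**Size at 20 v 20.** Fisher peaks at 2.53% (π about 0.34 or 0.66), with 2.3% at π = 0.41 and 1.2% at π = 0.10. Boschloo peaks at 4.64%.

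**Rejection regions.** Fisher rejects 214 tables and Boschloo 234. No table is rejected by Fisher alone. The 20 extra tables are these ten and their mirror images: 6 v 1, 8 v 2, 9 v 3, 12 v 5, 13 v 6, 14 v 7, 15 v 8, 17 v 11, 18 v 12, 19 v 14. For 18/20 v 12/20, Fisher p = 0.065 and Boschloo p = 0.039.

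**Power at 20 v 20.**

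| True rates | Fisher | Boschloo | Gain (points) |
|---|---|---|---|
| 90% v 60% | 49.2% | 60.9% | 11.7 |
| 80% v 50% | 40.9% | 49.2% | 8.3 |
| 70% v 40% | 34.7% | 44.7% | 9.9 |
| 40% v 10% | 49.2% | 60.9% | 11.7 |
| 30% v 5% | 44.6% | 54.4% | 9.8 |
| 92% v 41% | 93.1% | 95.9% | 2.8 |
| 41% v 0% | 95.8% | 95.8% | 0 |
| 20% v 0% | 37.0% | 37.0% | 0 |

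Hand check of the first row: the gain is the probability of the extra tables. At 90% v 60%:

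- 18 v 12: 0.2852 × 0.1797 = 0.0512
- 19 v 14: 0.2702 × 0.1244 = 0.0336
- 17 v 11: 0.1901 × 0.1597 = 0.0304
- 15 v 8: 0.0319 × 0.0355 = 0.0011
- the rest: about 0.0001

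The sum is 0.1165, or 11.7 points.

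The zero rows follow from the same list. Every extra table has at least one responder in each arm, so a true rate of 0% in one arm leaves nothing to gain.

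**Sensitivity to evaluable numbers.** These are the gains over the first five pairs, with the higher rate placed in either arm.

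| Evaluable | Fisher max size | Gain (points) |
|---|---|---|
| 20 v 20 | 2.5% | 8.3 to 11.7 |
| 19 v 19 | 2.8% | 3.9 to 11.9 |
| 20 v 19 | 3.6% | 0.0 to 4.3 |
| 20 v 18 | 3.5% | 1.7 to 7.3 |

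In every row Boschloo rejects all tables that Fisher rejects and its maximum size stays below 5%.

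**The case against.** The strongest reply is that nothing here is wrong. Fisher's test is valid, fully specified, familiar and conservative, it contradicts nothing in the Protocol, and it guarantees the level conditionally on the observed margins, which Boschloo's test does not. All of that stands. It makes this an efficiency point, and it rules out saying that the power is given up for nothing.

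The second reply is that the 8 to 12 points depend on balance. One missing assay in one arm cuts the gain to between 0 and about 4 points. Missing assays are plausible: the Swedish summary gives ELISPOT results for 37 of 38 vaccinees, and the Protocol's progress section gives 46 ELISPOT results when 57 volunteers had completed priming (although some of that gap may be timing). This also stands, and the size of the gain has to be quoted with it. It does not remove the point, because the gain is never negative.

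A reader might extend the point to adverse events, since the Safety data section uses the same test. The figures do not support that where it matters. The primary safety parameters are grade 3 or above; if such events occur in one arm only, for example 20% v 0%, both tests have 37.0% power. Comparisons with placebo behave the same way if no placebo volunteer responds.

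A reader might also infer that the trial asks whether the two routes are equivalent, because the Swedish summary says that a quarter "of the DNA given id primed equivalently to a 3.8mg dose given im". That is a preliminary result of another trial. The objectives here contain no equivalence aim, and the Protocol nowhere says that a non-significant difference will be read as similarity. An interval for the difference in responder rates is good reporting, but an analysis plan that is not shown may already provide it, so its absence is not a fault in the Protocol.

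**Conclusion.** The point holds as a modest efficiency improvement for the responder comparison between arms I and II. At 20 v 20 and an assumed two-sided 5% level, Fisher's test uses at most about half of the permitted error (2.5%), while Boschloo's stays within it (4.6%) and is at least as powerful for every pair of response rates. Expect about 8 to 12 points for the mid-range contrasts listed if both arms are complete, about 3 points at 92% v 41%, clearly less with unequal evaluable numbers, and nothing when one arm has a true rate of zero.

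The result rests on the assumed level and sidedness and on the chosen response rates. It does not show an error in the plan, does not carry over to rare adverse events, and does not show that the plan intends an equivalence claim.

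**What to change.** Before unblinding, replace Fisher's test in the Immunogenicity Data section by Boschloo's unconditional exact test for responder comparisons, and state the level as two-sided 5%. Preferably, report with each comparison the difference in proportions and its 95% confidence interval. Leave the Safety data section unchanged.

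The cost is one or two sentences, with no change to visits, samples or volunteers; the test is in standard software. The drawbacks are that it is less familiar and that it controls the error unconditionally and not conditionally on the margins. The change must be fixed before unblinding, because results such as 18/20 v 12/20 fall on different sides of 5% under the two tests.
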